### Training counselors

Two dental hygienists will be trained to deliver counseling to the second group (CE + MI) and third group (CE + MI + RA). Training materials have been prepared by referring to key MI literature and guide books [17,18], a dental MI workbook [27], and the interactive RA program (Cariogram) manual [23]. The training will be delivered by an expert panel composed of a health psychologist experienced in MI counseling and two public health workers specialized in dental interventions and caries risk assessment. The 12-hour training will be customized to involve key caries-related behaviors and typical scenarios commonly encountered in the dental settings. Training sessions will include lectures, discussions, demonstrations, and role plays. A hygienist will proceed to contact subjects only after demonstrating satisfactory competency as assessed by the panel using the Motivational Interviewing Treatment Integrity (MITI) Coding System [28] and a skill evaluation scheme on using Carigoram.

In each of the two groups (CE + MI and CE + MI + RA), participants will be randomly divided into two halves, who will be interviewed by the two counselors, respectively. To ensure the counseling is being delivered consistently with high fidelity to the MI principles, all counseling sessions will be audio-recorded and 20% of randomly selected sessions will be continuously reviewed and rated using the MITI coding system.

### Behavioral interventions

At baseline, different groups (CE, CE + MI, and CE + MI + RA) will receive their respective interventions.

(1) Conventional (oral health) education (CE)

The CE will be delivered to each parent through three pamphlets titled “Toothbrushing - your child can do it”, “Child’s diet and dental health”, and “Oral health care for your children” [29]. These color printed materials are in Chinese and were designed by the Oral Health Education Unit of the government Department of Health. Besides textual messages, there are pictorial illustrations for readers to better understand the information and advice.

(2) Motivational interviewing (MI)

The MI will be performed in an undisturbed room in the kindergarten. A typical MI counseling session will last for 15 to 30 minutes and will contain the following elements:

(i) Establish rapport: The MI session shall begin with showing concern and getting the parent to talk. The counselor may ask about the child’s kindergarten life, daily routines at home, family’s dental health, their contact with dentists and dental experience. The counselor may also encourage the parent to talk about his/her understanding about oral diseases and their impacts on one’s daily life.

(ii) Self-assess behaviors and identify discrepancy: The counselor will ask open-ended questions, listen carefully and encourage the parent to talk about the child’s dental habits and the parent’s dental wants/desires for the child, thereby identifying the discrepancy between the child’s present behaviors and important goals (in this case, the child’s oral health).

(iii) Elicit need for changes and promote self-efficacy: Once the counselor has identified the parent’s self-motivation for changing the child’s behavior(s), the counselor will explore and subtly encourage the changes that need to be made. The counselor will affirm the parent’s competence and encourage additional self-motivational statements (change talks). The counselor will also encourage the parent to talk about the difficulties in changing the child’s habits (the child’s temperament and resistance, parenting stress, time constraint, other family members’ influence, etc.) and explore possible solutions.

(iv) Present options and set goals: Once the parent shows a desire to improve the child’s behavior(s), the counselor will discuss the options, try to elicit commitment from the parent, and encourage him/her to talk about what change he/she would like and feels confident to try. Whenever the parent is ready for goal setting, a number of possible plans will be discussed in detail, so that a specific, measurable, and realistic goal can be set.

The whole MI session will be non-judgmental, respecting the parent’s expertise on his/her own child. The counselor shall avoid giving premature advice and be sensitive to the signals of resistance, such as arguing, interrupting, blaming others, and inattention. These signals imply that the parent is not ready to change at that moment and useful strategies will be to emphasize choices, avoid arguing, or recognize that the parent has a valid point.

(3) Interactive risk assessment (RA)

To obtain a reliable caries risk assessment result, children in the CE + MI + RA group will receive biological tests on saliva buffering capacity and abundance of caries-associated bacteria, *mutans Streptococci* and *Lactobacilli*[23]. Refraining from foods, drinks, and toothbrushing for at least 1 hour, children will be instructed to chew on a paraffin pellet for 5 minutes so that stimulated saliva can be collected. Dentobuff Strip, Dentocult SM Strip, and Dentocult LB kits (Orion Diagnostica, Finland) will be used and standard procedures will be followed in processing the samples. Before interviewing a parent in the CE + MI + RA group, the hygienist will gather the information previously collected through the questionnaire, oral examination, and biological tests, and enter it into the Cariogram program for caries risk assessment.

The RA is to be nested into the MI counseling and can be introduced at different stages of the MI session, depending on the parent’s response: (a) if the parent is not actively involved in the conversation, the interactive program can be used to break the ice, explain dental caries and its causes, and bring the parent into meaningful discussions; (b) after rapport is established, if the parent shows difficulty in recalling/assessing the child’s dental behaviors, the program can serve as a framework to assist his/her reflection and help him/her to identify the discrepancy between the child’s dental habits and parental expectation; (c) if the parent expresses willingness to make a change, the counselor can discuss with him/her the behavioral change(s) that would benefit the child the most and demonstrate how much risk reduction can be achieved; (d) if the parent feels the child is not ready for the suggested behavioral change, other options can be provided in a ‘menu’ format, listing all possible behavioral changes in various magnitudes and presenting their respective health gains. This approach would enable the child to make a start, which may have a knock-on effect leading to further improvements [30]; (e) the strategic use of the program enables the parent to make better informed decisions and set his/her own goal and agenda (what to change and to what extent).

As shown in Table 1, for both the CE + MI and the CE + MI + RA groups, after initial counseling, two brief follow-up telephone calls will be made to parents in these two groups to assist in the preparation for change, encourage the start, and discuss difficulties and possible solutions. To maintain the behavioral change and avoid relapse, each parent will be telephoned three more times up to 6 months after the initial contact [15].

**Table 1 T1:** Intervention activities (for CE + MI and CE + MI + RA groups)

**Activity**	**Time**	**Goals**
Initial counseling (X1)	Start of study	Establish rapport, discuss need and options, use strategies that structure and elicit change, and set goals
Follow-up telephone calls (X2)	2 weeks and 1 month after initial counseling	Assist preparation, encourage start, and solve problems
Maintenance telephone calls (X3)	2, 4, and 6 months after initial counseling	Promote maintenance, avoid relapse, and help re-establish change, if needed

CE, conventional (health) education; MI, motivational interviewing; RA, (caries) risk assessment.

### Benefits and risks of participation

Each participating child will receive a stationery kit (pencil, eraser and ruler costing around US$2) upon completing each oral health examination. The same stationery kit will also be given to each child who joined the screening. No monetary incentive will be provided. A written report on each child’s oral health status will be issued to his/her parents after each oral examination. At the end of the study, the children’s decayed teeth will be restored free of charge.

The risk of participating in this study is minimal, similar to that of routine dental checkups. No invasive procedures will be involved. Disposable materials and sterilized instruments will be used. Adverse events, if any, will be recorded and reported.

### Statistical analysis

Participants in the three intervention groups will be compared on their demographic background (age and gender), family socioeconomic status (parental education and family income), and baseline oral health behaviors and tooth status. The effectiveness of the intervention schemes will be evaluated and compared over 12 and 24 months through an intention-to-treat analysis, in which participants will remain in their originally assigned group regardless of the intervention actually received and subsequent withdrawal or deviation from the original intervention protocol [31]. For those who are lost to follow-up, the last assessment made will be considered valid throughout the study period.

The primary outcome will be caries increment in children and the proportion of caries-free children, measured by the number of new carious teeth (△dmft; continuous variable) and whether there are any new carious teeth (△dmft >0 or = 0; dichotomous variable). Secondary outcomes will be changes in parental efficacy in protecting children’s oral health and changes in children’s dental behaviors (outcome variables described in Table 2). Effect sizes (relative risk) and their confidence intervals will be calculated. Chi-square tests will be used for comparing proportions; means will be compared through parametric or non-parametric methods, as appropriate. Number needed to treat, calculated as 100 divided by the risk difference expressed as a percentage [32], will be presented to provide an estimate of the number of parents needed to be counseled in order to avoid one child with new dental caries.

**Table 2 T2:** Outcome variables

**Outcomes**	**Variables**	**Codes**	**Source of information**

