## Methods/Design

### Sample size calculation

The main outcome of this study will be any caries increment or not (change in decayed, missing, and filled teeth (△dmft >0 or = 0) in the study children. Our latest survey showed that about 35% of Hong Kong children aged 3 years develop new caries in one or more teeth (△dmft >0) in a year [24]. An intervention will be considered to have a clinically significant effect if it reduces this rate to 20% in a year. Such a magnitude of effect size (relative risk of 0.57) was also reported by a previous MI trial in infants [15]. In order to detect such a reduction at a significance level of 5% and a statistical power of 80%, 184 parent-child dyads per group will be needed (multiple comparisons considered). Allowing for a 20% attrition rate, 230 parent-child dyads would need to be recruited into each of the three study groups. The total sample size will be 690.

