### Oral health assessment

All participants will be assessed at baseline and followed-up after 12 and 24 months, so that the outcomes of the interventions can be determined.

A questionnaire (in Chinese) pre-tested in our previous study [24] will be completed by parents to gather information on (i) family socio-demographic background, (ii) parental knowledge of and attitudes toward oral health, (iii) parental efficacy in protecting the child’s oral health, (iv) child’s oral health behaviors (diet and oral hygiene), and (v) child’s history of dental treatment and use of caries-preventive agents, such as topical fluorides.

All child participants will undergo a dental examination. The examiner has been trained regarding the diagnostic criteria and examination methods and will be further calibrated against an experienced oral epidemiologist to ensure an agreement rate over 90%. Duplicate examinations will be carried out on 10% of the subjects, for assessing the intra-examiner reliability. Each child will be examined in the supine position. A mouth mirror, illuminated by an intra-oral LED light, and a community periodontal index (CPI) probe will be used. The status of each tooth surface will be assessed by visual inspection, aided by tactile inspection if necessary. No radiographs will be taken. The WHO recommended diagnostic criteria for dental caries will be followed - that is, caries will be recorded as present when a lesion in a pit or fissure, or on a smooth tooth surface, has an unmistakable cavity, undermined enamel, or a detectably softened floor or wall [25].

The oral hygiene status will be evaluated using the Silness-Löe Plaque Index [26]. The examiner will be blinded to the group allocation of each child subject throughout the whole study.

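### Carrying the last assessment forward scores every child lost before 12 months as having no new caries, so absolute caries rates are understated and unequal loss can bias the comparison in either direction

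*Protocol article*

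**What the plan says.** The Statistical analysis section plans an intention-to-treat comparison in which "participants will remain in their originally assigned group regardless of the intervention actually received and subsequent withdrawal or deviation". It then gives the only missing-data rule in the document: "For those who are lost to follow-up, the last assessment made will be considered valid throughout the study period".

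The Oral health assessment section sets the visits: "All participants will be assessed at baseline and followed-up after 12 and 24 months". No dental examination is scheduled between baseline and month 12.

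Table 2 defines the primary outcome through three variables: the number of new carious teeth (change in dmft), whether there are any (change above 0 or not), and whether the child is caries free (dmft 0 or not). The effect measure named in the text is the relative risk. The NNT, computed from the risk difference, will also be presented.

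The Sample size calculation section assumes that "about 35% of Hong Kong children aged 3 years develop new caries in one or more teeth" in a year, and calls an intervention clinically significant "if it reduces this rate to 20% in a year". It asks for 184 evaluable dyads per group and adds: "Allowing for a 20% attrition rate, 230 parent-child dyads would need to be recruited into each of the three study groups".

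**The concern.** For a child with no examination after baseline, the value carried forward is the baseline dmft, so the change is exactly 0. The child enters the analysis as a success at 12 and at 24 months. A child seen at 12 but not at 24 months is assigned no caries in the second year.

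The article does not itself call caries irreversible. However, dmft adds decayed, missing and filled teeth, and decay is recorded only at cavitation, so over two years the true count essentially only rises. The rule thus assumes no progression in any lost child, while the sample size section expects about 35% of 3-year-olds to develop new caries within one year.

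Two things are at stake. Whenever children are lost, the reported caries rates and mean increments are too low, and the risk difference and NNT are distorted with them. Where loss differs between arms, the comparison itself is biased. Different loss is plausible because only the two MI arms receive counselling and five telephone calls (Table 1).

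**Working it through.** **Inputs from the document.** Control risk 35% and intervention risk 20% in a year; 5% significance; 80% power; 184 evaluable and 230 recruited per group; 20% attrition.

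**Assumptions, not in the document.** Two-sided tests; alpha 0.05/3 for three pairwise comparisons (the text says only that multiple comparisons were considered); all timing of loss and all splits of loss by arm; loss unrelated to outcome.

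**1. The plan's own figure.** With pooled variance under the null and no continuity correction,

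n = [z_α √(2p̄(1−p̄)) + z_β √(p₁(1−p₁) + p₂(1−p₂))]² / (p₁−p₂)²,

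with p₁ = 0.35, p₂ = 0.20, p̄ = 0.275, z_α = 2.394 and z_β = 0.842, n = 184.2. This is 185 when rounded up, against 184 stated. Power at 184 is 79.96%. Then 184/0.80 = 230, and 3 × 230 = 690. The stated sample size reproduces.

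**2. Carry-forward at 12 months, equal loss.** If a share d is lost before 12 months and scored as no new caries, the analysed rate is p × (1 − d), with all 230 in the denominator. For d = 20%: 0.35 × 0.80 = 0.28 and 0.20 × 0.80 = 0.16.

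| Loss by 12 months | Analysed rates | Risk difference | NNT | RR | Power, carry-forward, n = 230 | Power, observed children only |
|---|---|---|---|---|---|---|
| 0% | 35% vs 20% | 15 points | 6.7 | 0.57 | 89.0% | 89.0% (230) |
| 10% | 31.5% vs 18% | 13.5 points | 7.4 | 0.57 | 83.5% | 85.0% (207) |
| 20% | 28% vs 16% | 12 points | 8.3 | 0.57 | 76.4% | 80.0% (184) |
| 30% | 24.5% vs 14% | 10.5 points | 9.5 | 0.57 | 67.9% | 73.5% (161) |

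Mean change in dmft shrinks by the same factor (1 − d). The relative risk of new caries does not move because the factor cancels. In every row with loss, carry-forward has less power than analysing only the children who were seen.

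**3. Carry-forward at 24 months.** Assume a constant annual risk, with 10% lost before 12 months and 10% between 12 and 24 months. The true two-year risks are 1 − 0.65² = 57.8% and 1 − 0.80² = 36.0%. The analysed rates are 0.80 × 0.5775 + 0.10 × 0.35 = 49.7% and 0.80 × 0.36 + 0.10 × 0.20 = 30.8%. The risk difference falls from 21.8 to 18.9 points, and the relative risk is 0.62 before and after.

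**4. Unequal loss before 12 months (230 per arm, assumed rates).**

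| True risks, CE / MI | Loss, CE / MI | Analysed rates | Analysed RR | Rejection at 0.05/3 | Rejection at 0.05 |
|---|---|---|---|---|---|
| 35% / 35% (no effect) | 10% / 25% | 31.5% vs 26.3% | 0.83 | 12.4% | 23.7% |
| 35% / 35% (no effect) | 15% / 25% | 29.8% vs 26.3% | 0.88 | 6.0% | 13.3% |
| 35% / 20% (RR 0.57) | 25% / 10% | 26.3% vs 18% | 0.69 | 40% (power) | 57% (power) |

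The first two rows should reject 1.7% of the time at 0.05/3 and 5% at 0.05. In the third row, a real effect at the planned size is mostly missed.

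**5. The caries-free variable.** If dmft cannot fall, a child with baseline dmft above 0 can never become caries free, so carrying the baseline value forward classifies that child correctly. Only children with baseline dmft = 0 are misclassified by the rule.

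**The case against.** Much of the case on the other side stands.

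- **Relative effect.** A reader might infer that carry-forward dilutes the treatment effect in general. It does not: under equal loss unrelated to outcome, the relative risk of new caries, which is the named effect measure, stays at 0.57. What shrinks is the risk difference, mean change in dmft and power, and the NNT rises.
- **Direction.** It is tempting to say that the rule favours MI, or that it is never conservative. Equal loss shrinks the risk difference, which is conservative for a superiority claim. With unequal loss, the document gives no rates by arm. The extra calls could aid retention in the MI arms as easily as burden them, and the examinations, gifts, reports and free restorations at the end of the study are common to all arms.
- **Power.** The 76% needs all 20% to be lost before 12 months, and the article does not say when loss occurs. With 10% lost by then, power is 83.5%, above the planned 80%. At 24 months, with the rates in step 3, it is about 96%.
- **Sample size.** A reader might see a contradiction between 184 evaluable and 230 analysed. It is only a mismatch: the allowance is an ordinary one and reproduces. It treats lost children as giving no information, while the analysis enters them as non-events.
- **Level of detail.** An imputation model and sensitivity analyses may properly sit in an analysis plan that is not shown, so their absence is no fault.

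None of this rescues the rule itself. It is stated, not omitted, and an analysis plan that followed the article would inherit it.

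**Conclusion.** The concern holds in a limited form. As the main rule, carry-forward assigns zero new caries to children whom the plan itself expects to develop it at about 35% a year in the absence of an effect. Absolute caries rates and mean change in dmft are therefore understated in any arm that loses children. With equal loss, the risk difference and power fall and the NNT rises. At the extreme of 20% lost before 12 months, the cost is 3 points of risk difference and about 4 points of power relative to analysing the observed children. The relative risk survives equal loss.

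Unequal loss is the more serious exposure because the type I error is then not protected: about 12% instead of 1.7% in the 10% vs 25% example. The reverse pattern can hide a real effect. These loss rates, the timing of loss and the alpha of 0.05/3 are assumptions. The documents do not support a claim that the trial will show a false benefit, or that its sample size is wrong.

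**What to change.** Replace the carry-forward sentence as the main rule. One option is multiple imputation, done separately by arm, of 12- and 24-month dmft from baseline dmft, any 12-month dmft and the stratification factors, with no imputed value below the last one observed. The other is a likelihood or grouped-time model for new caries that uses all observed visits. Keep carry-forward only as a labelled sensitivity analysis, and report loss by arm and by visit beside it. A further analysis that departs from missing at random would be useful but is optional.

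The cost is a change of wording, some programming, and reliance on a missing-at-random assumption for the main result. No extra data are needed. The Trial status section says that recruitment has not started, so the change can be made before any outcome exists.

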**Change in child’s dental behavior**			
Diet	Frequency of snacking per day	(1) Decreased;	Questionnaire
		(2) No change;	
		(3) Increased	
Oral hygiene	Frequency of toothbrushing per day	(1) Decreased;	Questionnaire
		(2) No change;	
		(3) Increased	
	Silness-Löe Plaque Index	Continuous	Dental examination

* dmft refers to decayed, missing, and filled teeth.

**Parental efficacy was measured using five-point Likert scale questions (“strongly agree”, “agree”, “neutral”, “disagree”, and “strongly disagree”).

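### On its natural reading, the plan compares the Plaque Index on mean change from baseline; adjusting for baseline plaque would be more precise at no cost

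*Protocol article*

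**What the plan says.** All references are to the protocol article.

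- **Form of the outcome.** Statistical analysis says: "Secondary outcomes will be changes in parental efficacy in protecting children’s oral health and changes in children’s dental behaviors". In Table 2 the row "Silness-Löe Plaque Index" stands under the heading "Change in child’s dental behavior". It is coded as continuous, with the dental examination as its source.
- **Method.** The same section says: "Chi-square tests will be used for comparing proportions; means will be compared through parametric or non-parametric methods, as appropriate". It names no model and no covariate for any outcome.
- **Measurement.** Oral health assessment says: "The oral hygiene status will be evaluated using the Silness-Löe Plaque Index". It adds: "The examiner will be blinded to the group allocation of each child subject throughout the whole study". On timing it says: "All participants will be assessed at baseline and followed-up after 12 and 24 months". A baseline plaque value is therefore available.
- **Other secondary variables.** The remaining four in Table 2 are questionnaire items coded as decreased, no change or increased.
- **Randomization.** It is stratified by parental education and baseline dmft, not by plaque.

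**The concern.** Read together, the outcome sentence, the table heading and the method sentence lead to a between-group test of mean change in plaque. If the non-parametric option were taken, the usual rank test on change would also carry no covariate.

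A change score subtracts the whole baseline value. Plaque scores taken 12 or 24 months apart in preschool children are unlikely to track each other closely. Where they do not, full subtraction adds baseline noise to the outcome. It also lets the arm that happens to start with more plaque show a larger apparent fall, through regression to the mean.

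At stake is the precision of the one secondary outcome that does not come from the parent questionnaire. The Discussion describes the cognitive and behavioral outcomes as self-reported and subjective, so the examiner's plaque score is useful evidence on whether oral hygiene changed.

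**Working it through.** **The plan's own figure.** No standard deviation, target effect or power is given for plaque. The only calculation is for any caries increment, 35% against 20%, and it supplies the group size used below. With two-sided α = 0.05/3 (my reading of the statement that multiple comparisons were considered) and 80% power:

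n = [2.394·√(2·0.275·0.725) + 0.842·√(0.35·0.65 + 0.20·0.80)]² / 0.15² = 184.2, or 185 when rounded up, against the stated 184.

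Then 184/0.8 = 230 and 3 × 230 = 690, as stated. This reproduces the caries calculation and says nothing about plaque.

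**Assumptions.** Equal standard deviation (SD) at baseline and follow-up, a baseline to follow-up correlation ρ of 0.3 to 0.8, and 184 analysed per group. Only the 184 comes from the document.

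**Formulas, in SD units**

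- Variance of the change score: 2(1 − ρ)
- Variance after linear adjustment for baseline: 1 − ρ²
- Adjusted divided by change: (1 + ρ)/2
- Standard error (SE) of a two-group contrast: √(variance × 2/184)
- Shift of the change contrast for a chance baseline difference D: −(1 − ρ)D

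| ρ | Variance ratio | SE, change | SE, adjusted | Excess SE of change | n per group giving the adjusted analysis the same precision | Size of shift for D = 0.1 SD |
|---|---|---|---|---|---|---|
| 0.3 | 0.65 | 0.123 | 0.100 | 24% | 120 | 0.07 SD |
| 0.5 | 0.75 | 0.104 | 0.090 | 15% | 138 | 0.05 SD |
| 0.7 | 0.85 | 0.081 | 0.075 | 8.5% | 156 | 0.03 SD |
| 0.8 | 0.90 | 0.066 | 0.063 | 5.4% | 166 | 0.02 SD |

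A baseline difference of 0.1 SD is about one standard error, since √(2/184) = 0.104.

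**In terms of power (illustration only).** Take an effect for which the change-score test has 80% power at two-sided 5%. The adjusted test then has power Φ(2.802/√ratio − 1.960), which is 93.5%, 89.9%, 86.0% and 84.0% at ρ = 0.3, 0.5, 0.7 and 0.8. The starting 80% is my choice; the plan makes no power claim for plaque.

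**Error rate given the baseline imbalance, at ρ = 0.5.** The change test rejects when the contrast exceeds 1.96 × 0.1043 = 0.204 SD in size. Given D, the contrast has standard error 0.0903.

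- D = 0: the threshold is 0.204/0.0903 = 2.26, and the rejection rate is about 2.4%.
- D = 0.2 SD: the mean shifts by 0.10/0.0903 = 1.11, and the rate is about 12.4%.
- Over all values of D the rate averages 5%. A difference of 0.2 SD or more is 0.2/0.1043 = 1.92 standard errors, which occurs in about 1 trial in 18 for a given pair of arms.

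**Effect of carrying the last assessment forward.** A child lost before 12 months contributes the baseline value as follow-up. As an extreme case, suppose that all 20% attrition falls there, that losses are unrelated to plaque, and that mean plaque is stable. The working correlation is then 0.8ρ + 0.2, or 0.44, 0.60, 0.76 and 0.84. The variance ratios become 0.72, 0.80, 0.88 and 0.92. Taking 1/√ratio − 1, the excess standard error falls to about 18%, 12%, 7% and 4%.

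**The case against.** The strongest reply is that the article fixes no test. It never says the comparison is unadjusted, and a baseline-adjusted linear model is itself a parametric comparison of means. Table 2 writes a delta for dmft but none in the plaque row, so the change form comes only from the block heading and the outcome sentence. Covariates for a secondary outcome are often left to an analysis plan, and none is shown. This stands: a reader might infer that an unadjusted analysis is prescribed, and the text does not support that. What remains is that the outcome is called a change and only a comparison of means is named, so the less efficient analysis is the natural reading.

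Other tempting readings also fail.

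- **That the change score is biased or inflates type I error.** Randomization keeps it unbiased on average, with an overall 5% level. The 12.4% figure applies to one uncommon imbalance and must be read beside 2.4% at zero imbalance.
- **That subtraction is right only at perfect correlation.** It is optimal when the regression slope of follow-up on baseline is 1. The slope equals the correlation only under equal variances.
- **That nothing in the design balances plaque.** Individual 1:1:1 randomization balances it in expectation. Only chance imbalance remains.
- **That plaque is the trial's only objective check.** The caries examination, made by the same blinded examiner, is also a clinical outcome.

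It is also fair to say that the size of the gain rests entirely on an assumed correlation.

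**Conclusion.** The point holds as a free improvement to one secondary outcome. On the natural reading, plaque is compared on mean change without baseline plaque as a covariate. That is valid but less precise than it need be.

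For assumed correlations of 0.3 to 0.8 with equal variances, the standard error is about 24% to 5% too large. The loss is smaller if many values are carried forward, and small in any case if plaque tracks strongly over time. A chance baseline difference moves the estimate by 0.7 to 0.2 of its size over the same range.

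No primary conclusion depends on this, and the documents do not support calling it a fixed error or a source of systematic bias.

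**What to change.** In Statistical analysis, add one sentence: the Plaque Index at 12 and at 24 months will be compared between groups by a linear model of the follow-up value on group and baseline Plaque Index, reporting adjusted mean differences with confidence intervals. The stratification factors (parental education and baseline dmft) may be added as covariates. In Table 2, relabel the row as the Plaque Index at 12 and 24 months, adjusted for baseline.

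The cost is one sentence and one table entry. No new data, visits or staff are needed. Trial status says that recruitment has not begun, so the choice can be fixed before any outcome is seen.
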